## Abstract

**Background:**

Most patients with heart failure are diagnosed and managed in primary care, however, underdiagnosis and undertreatment are common. We assessed whether implementation of a diagnostic-therapeutic strategy improves functionality, health-related quality of life, and uptake of heart failure medication in primary care.

**Methods/Design:**

A selective screening study followed by a single-blind cluster randomized trial in primary care. The study population consists of patients aged 65 years or over who presented themselves to the general practitioner in the previous 12 months with shortness of breath on exertion. Patients already known with established heart failure, confirmed by echocardiography, are excluded. Diagnostic investigations include history taking, physical examination, electrocardiography, and serum N-terminal pro B-type natriuretic peptide levels. Only participants with an abnormal electrocardiogram or an N-terminal pro B-type natriuretic peptide level exceeding the exclusionary cutpoint for non-acute onset heart failure (> 15 pmol/L (≈ 125 pg/ml)) will undergo open-access echocardiography. The diagnosis of heart failure (with reduced or preserved ejection fraction) is established by an expert panel consisting of two cardiologists and a general practitioner, according to the criteria of the European Society of Cardiology guidelines.

Patients with newly established heart failure are allocated to either the 'care as usual’ group or the 'intervention’ group. Randomization is at the level of the general practitioner. In the intervention group general practitioners receive a single half-day training in heart failure management and the use of a structured up-titration scheme. All participants fill out quality of life questionnaires at baseline and after six months of follow-up. A six-minute walking test will be performed in patients with heart failure. Information on medication and hospitalization rates is extracted from the electronic medical files of the general practitioners.

**Discussion:**

This study will provide information on the prevalence of unrecognized heart failure in elderly with shortness of breath on exertion, and the randomized comparison will reveal whether management based on a half-day training of general practitioners in the practical application of an up-titration scheme results in improvements in functionality, health-related quality of life, and uptake of heart failure medication in heart failure patients compared to care as usual.

**Trial registration:**

ClinicalTrials.gov NCT01202006

## Background

Heart failure (HF) is an emerging epidemic in the elderly, causing high mortality rates, substantial loss in quality of life, and high healthcare costs [1]. The last two decades, progress in patient management, including multiple drug therapies and implantable devices, has improved prognosis of patients with heart failure with reduced ejection fraction (HF-REF) [2,3]. Poor compliance to and insufficient up-titration of evidence-based medication is a major contributor to hospital (re)admissions and loss of life years in these patients [4]. Angiotensin converting enzyme (ACE) inhibitors, angiotensin receptor blockers (ARBs) and beta-blockers did not show a significant beneficial effect in patients with heart failure with preserved ejection fraction (HF-PEF) [5], and their prognosis did not improve over the last years [6]. Currently, adequate treatment of hypertension and other comorbidities, control of heart rate in those with concurrent atrial fibrillation, and diuretics to control sodium and water retention are considered important in HF-PEF [4].

The majority of the elderly patients with HF is diagnosed and managed in primary care [7]. Unfortunately however, recognizing HF in the early stage is challenging, and echocardiography is not readily available in primary care. A diagnosis based on the signs and symptoms only, without echocardiography, results in both false-positive [8,9] and false-negative diagnoses [10]. Moreover, uncertainty about HF diagnosis and fear of side effects have led to underutilization of ACE-inhibitors and beta-blockers in patients with HF in primary care [11,12].

We suspect that especially in older persons presenting with shortness of breath to the general practitioner (GP), the prevalence of undetected HF is high. Therefore, we developed a selective screening strategy, including an open-access outpatient echocardiography facility. In addition we developed an easy to apply up-titration scheme for those newly diagnosed with HF-REF and HF-PEF. Our main objective is to assess whether such a targeted diagnostic-therapeutic approach improves current underdiagnosis and undertreatment.

### Key objectives

– To determine the prevalence of unrecognized heart failure (HF-REF, HF-PEF, and isolated right sided heart failure) in elderly who present themselves with shortness of breath on exertion to the general practitioner.

– To examine the effect of treatment guided by a structured up-titration scheme on functionality, health-related quality of life, and uptake of heart failure medication in patients with newly, screen-detected HF.

– To assess the cost-effectiveness of such an intervention.

## Methods/Design

### Study design

Our design consists of two parts. The first part is a selective screening study (case finding) of HF in elderly with shortness of breath on exertion. The second part is a single-blind, cluster randomized controlled trial comparing an intervention at the level of the GP to improve treatment uptake with care as usual in those with screen-detected HF. The intervention consists of a half-day training in the management of HF, and the practical application of an up-titration scheme for HF-REF and HF-PEF separately. See Figure 1 for the study flowchart.

**Figure 1 F1:**
[figure not shown]
**Flowchart STRETCH – study.** GP = general practitioner, EMF = electronic medical file, HF = heart failure, IC = informed consent, NTproBNP = N-terminal pro B-type natriuretic peptide.

### Study population and recruitment

Thirty primary care practices in the Zeist region, located in the vicinity of the Diakonessenhuis hospital Zeist, the Netherlands, participate in this study. In this sample of primary care practices, urban, suburban and rural communities are represented.

The study population consists of persons aged 65 years or over who in the previous 12 months presented themselves to one of the participating GPs with shortness of breath on exertion (including those known with a pulmonary disease), irrespective of whether they were suspected of HF or not. Shortness of breath was not necessarily the main reason for contact. Eligible subjects are identified from the electronic medical files of the participating GPs by a single physician ([name]).

Patients already known with an established diagnosis of HF confirmed by a cardiologist with help of an echocardiography are excluded, as are patients with a life expectancy shorter than 6 months, and those unable to give informed consent.

We consider our study sample representative for elderly aged 65 years or over in the community, since in the Netherlands all citizens, except those living in a nursing home or hospice, are registered with a GP, irrespective of (co)treatment by a specialist.

### Randomization and blinding

Random allocation to either management guided by a structured up-titration scheme (intervention group) or care as usual (control group) will be executed at the level of the GP. As a result, patients with HF of one and the same GP (a cluster) will all be managed according to the same arm. This approach was taken to reduce the risk of contamination between patient groups.

Since it is not deemed feasible to keep the GPs in the care as usual group unaware of the existence of an intervention arm, blinding of the participants is considered necessary to minimize bias in assessing the outcome parameters. In addition, the researcher performing the six minutes walking test is blinded to the patient’s allocation arm. The risk of observer bias for the other endpoints is minimized, because questionnaires on quality of life are filled out at home by the participants themselves, and retrieving information on HF medication and HF related doctor appointments from the electronic medical files is not subject to interpretation.

### Sample size

The difference in mean distance walked during the six-minute walking test (6MWT) between the two groups after six months follow-up will be taken as the primary outcome. The average distance walked by HF patients ranges from 242 m (standard deviation 71 m) up to 427 m (standard deviation 100 m), depending on the severity of HF [13]. Since it was shown that an increase of 50 m in walking distance indicated a clinically relevant change [14,15], we consider a mean difference of 50 meters between groups as the minimal important difference to show an effect of the intervention.

We used the two-sample t-test power analysis to examine how many HF patients are needed per group to demonstrate an effect. With an effect size of 0.6, alpha of 0.05, and beta of 0.2, group sample sizes of two times 45 will be sufficient.

We assume that in a standard general practice with 2400 patients, at least 50 patients aged 65 years or over will experience shortness of breath during a one-year period. The prevalence of previously unrecognized HF in such patients is expected to be around 14% (10.4-17.5%) [16]. With a participation rate of 50%, a mean number of 3.5 patients per GP are expected to have newly detected HF (50% HF-REF and 50% HF-PEF). Twenty-six general practitioners are needed to reach the targeted number of HF patients. We will include 4 extra practices to allow for taking clustering into account.

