### Results of inclusion

Thirty GPs are included in the study, 14 were randomized to the care as usual arm and 16 to the intervention arm. We invited 1,527 elderly patients with shortness of breath on exertion to participate in the study. Of the invited patients, 77% responded, and eventually 38% was willing to participate. Reasons named for non-participation were; expected burden too high (40%), already known to a cardiologist (24%), other demanding health problems (15%), not experiencing shortness of breath anymore (12%), and severe immobility (5%).

Finally, 585 patients signed informed consent and were included in our study. The mean age of the participants was 74.1 (SD ±6.3) years. Stratified by age, 57% was aged between 65 and 74 years, 37% between 75 and 84 years, and 6% was aged 85 years or over. The percentage females was 54.5%. Important comorbidities were pulmonary disease (55.2%), hypertension (53%), hypercholesterolemia (32%), and ischemic heart disease (20%). The 14 GPs in the care as usual arm yielded 351 participants, and the 16 GPs of the up-titration arm 234 participants. Baseline characteristics of included patients divided between both groups are described in Table 1.

**Table 1 T1:** Baseline characteristics of the 585 participants, divided in the intervention and care as usual group

**Characteristics**	**All**	**Care as usual**	**Intervention***	
	**n = 585**	**n = 351 (60%)**	**n = 234 (40%)**	**p-value**
General				
Mean age in years ± sd	74.1 ± 6.3	73.8 ± 6.1	74.4 ± 6.5	0.25
Female sex	319 (54.5)	181 (51.6)	138 (59.0)	0.08
MRC dyspnea score ≥ 3	157 (26.8)	97 (27.6)	60 (25.6)	0.59
Cardiovascular comorbidities				
Ischemic heart disease	116 (19.8)	70 (19.9)	46 (19.7)	0.93
Prior myocardial infarction	43 (7.4)	27 (7.7)	16 (6.8)	0.70
Prior PCI/CABG	47 (8.0)	29 (8.3)	18 (7.7)	0.80
Vascular comorbidity	351 (60.0)	217 (61.8)	134 (57.3)	0.27
Hypertension	310 (53.0)	196 (55.8)	114 (48.7)	0.09
Hypercholesterolemia	187 (32)	115 (32.8)	72 (30.8)	0.61
Diabetes Mellitus	79 (13.5)	47 (13.4)	32 (13.7)	0.92
Prior stroke or TIA	51 (8.7)	27 (7.7)	24 (10.3)	0.28
Peripheral arterial disease	35 (6.0)	22 (6.3)	13 (5.6)	0.72
Atrial fibrillation	42 (7.2)	33 (9.4)	9 (3.8)	0.01
Non-cardiovascular comorbidities				
Cognitive disorders	110 (18.8)	50 (14.2)	60 (25.6)	0.001
Asthma/COPD	323 (55.2)	200 (57.0)	123 (52.6)	0.29
Depression	72 (12.3)	39 (11.1)	33 (14.1)	0.28
Medication				
Loop diuretics	55 (9.4)	36 (10.3)	19 (8.1)	0.39

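### At the planning prevalence of 14%, the reported recruitment projects about 82 heart failure patients (49:33), so the planned 90 and 80% power are unlikely to be met and should be restated

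*Protocol article*

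**What the plan says.** The Sample size section of the protocol article names the test: "We used the two-sample t-test power analysis to examine how many HF patients are needed per group to demonstrate an effect". The target difference follows: "we consider a mean difference of 50 meters between groups as the minimal important difference to show an effect of the intervention". The result is given as "With an effect size of 0.6, alpha of 0.05, and beta of 0.2, group sample sizes of two times 45 will be sufficient".

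The yield per practice rests on at least 50 eligible patients, a 14% prevalence of unrecognised HF (10.4% to 17.5%) and the participation rate: "With a participation rate of 50%, a mean number of 3.5 patients per GP are expected to have newly detected HF". This leads to 26 GPs. Then: "We will include 4 extra practices to allow for taking clustering into account".

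The Results of inclusion section of the same article reports 30 GPs and 1,527 invited patients. "Of the invited patients, 77% responded, and eventually 38% was willing to participate". In all, 585 were included. By arm: "The 14 GPs in the care as usual arm yielded 351 participants, and the 16 GPs of the up-titration arm 234 participants". It does not say how many of the 585 have HF.

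**The concern.** The sample size paragraph and the inclusion figures stand in one article and are not reconciled. The number of practices was derived from 50% participation, and the realised figure is 38%. The planned groups were equal, and the participants are split 60:40. Nothing in the article tells the reader what this does to the expected number of HF patients or to power.

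The primary outcome is judged against a 50 m difference. If 80% power is taken at face value, a non-significant result could be read as evidence against a 50 m effect when the trial was less able to detect it than stated.

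**Working it through.** **1. The plan's own figures.** Inputs, all from Sample size: d = 0.6, alpha 0.05 (two-sided reproduces the figure), power 80%, 50 eligible per practice, 50% participation, 14% prevalence.

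- Two-sample t-test, noncentral t: 44 per group gives power 0.795 and 45 gives 0.804. So 45 per group, 90 in total, is right.
- Yield per GP: 50 × 0.50 × 0.14 = 3.5. GPs needed: 90 / 3.5 = 25.7, so 26.
- With the 4 extra practices: 30 × 3.5 = 105 patients.
- Room for clustering: 105 / 90 = 1.167. Setting 1 + (3.5 − 1) × ICC = 1.167 gives ICC = 0.067, if no patient is lost.

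**2. Recruitment as reported.** Inputs from Results of inclusion.

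- Invited per practice: 1,527 / 30 = 50.9, as planned.
- Participation: 585 / 1,527 = 38.3%, against 50%.
- Participants per practice: 585 / 30 = 19.5, against 25.

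**3. Projected HF patients and power.** The prevalence is the plan's, assumed equal in both arms. Power is from the noncentral t at d = 0.6, with noncentrality 0.6 / √(1/n1 + 1/n2).

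| Prevalence | HF patients (585 × p) | Usual care (351 × p) | Intervention (234 × p) | Power |
|---|---|---|---|---|
| 10.4% | 60.8 | 36.5 | 24.3 | 0.62 |
| 14% | 81.9 | 49.1 | 32.8 | 0.75 |
| 17.5% | 102.4 | 61.4 | 41.0 | 0.84 |

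Reaching 90 patients needs 90 / 585 = 15.4% prevalence. At a 60:40 split, 80% power needs about 93 patients, or 93 / 585 = 15.9%. The imbalance itself costs little: 41:41 gives 0.77 against 0.75 for 49:33. Most of the shortfall is the lower participation.

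**4. Clustering and loss.** The article gives no ICC or loss rate, so these values are assumptions. Design effect per arm is 1 + (m − 1) × ICC, with m = 49/14 = 3.5 and 33/16 = 2.06.

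| ICC | No loss | 10% loss | 20% loss |
|---|---|---|---|
| 0.01 | 0.74 | 0.70 | 0.64 |
| 0.05 | 0.71 | 0.67 | 0.62 |
| 0.10 | 0.68 | 0.64 | 0.58 |

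**5. Standard deviation.** 50 m at d = 0.6 implies SD = 50 / 0.6 = 83 m, inside the quoted range: "The average distance walked by HF patients ranges from 242 m (standard deviation 71 m) up to 427 m (standard deviation 100 m". For 49:33 before clustering and loss, power for 50 m is 0.87 at SD 71 m, 0.75 at 83 m and 0.59 at 100 m. The standardised difference detectable with 80% power is 0.639, which is 53 m at SD 83 m and 64 m at SD 100 m.

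**6. Baseline adjustment.** With correlation r between baseline and six-month distance (assumed), d becomes 0.6 / √(1 − r²). For 49:33 before clustering and loss, r = 0.4 gives 0.82, r = 0.5 gives 0.86 and r = 0.6 gives 0.91.

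**The case against.** The strongest reply is that nothing in the Sample size paragraph is miscalculated. That stands. Every figure reproduces, and the design as planned projected 105 patients with some room for clustering. A participation rate that turned out lower than assumed is a recruitment outcome, not a false statement in the plan. A reader might infer an arithmetic error, or a design that could never deliver its size; the documents support neither.

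A reader might also take 82 as the number of HF patients in the trial. The article gives no such count. The figure needs the 14% planning prevalence and the assumption that it is equal in both arms. A prevalence of 15.4%, inside the stated range, already reaches 90.

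Nor do the documents show that the SD is 100 m. That is one end of the quoted range, and the implied 83 m lies near its middle. Whether screen-detected patients resemble the better-walking group is not stated.

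Two further replies have weight. An article may leave the ICC and the loss rate to the full protocol, so their absence is not the point here; the point is that printed figures no longer fit together. And the Statistical analyses section plans a multilevel analysis with ANCOVA, which could recover the lost power. But the stated 80% belongs to an unadjusted t-test, and that section refers only to relevant baseline parameters without naming the walking distance.

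**Conclusion.** The point holds as a projection. At the article's own planning prevalence, the reported recruitment falls about 8 patients short of 90 and gives about 75% power for the stated test, where 80% is claimed. The 15 patients by which the plan exceeded its minimum are probably used up before clustering, drop-out or the referral of patients with a potentially treatable cause (Intervention section) is counted. All three can only lower unadjusted power further.

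It is not certain. At the top of the prevalence range, 80% is still met before those losses, and adjustment for baseline distance could restore it at moderate correlations. The conclusion rests on equal prevalence in both arms and on d = 0.6; it does not depend on any particular ICC, loss rate or the 100 m SD.

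**What to change.** Keep the existing calculation as the planning basis, and add a short restatement for the trial as recruited:

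- HF patients per arm: the actual count if known, otherwise the projection of 49:33 with the range 61 to 102 in total.
- The resulting power or detectable difference (about 53 m at SD 83 m and 64 m at SD 100 m for 49:33, before clustering and loss), with the ICC, the loss rate and an SD range of 71 to 100 m given as stated assumptions.
- In Statistical analyses, name the baseline six-minute walking distance as a covariate in the multilevel ANCOVA. It is already measured in HF patients, so this adds no data collection.
- A statement that the primary result will be interpreted through its confidence interval against 50 m.

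The cost is one added paragraph, one named covariate and a less favourable stated power. No extra enrolment is asked for.

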Only participants with an abnormal ECG or an elevated blood NTproBNP level will undergo additional echocardiography in the outpatient clinic of the Diakonessenhuis Hospital Zeist. Echocardiography is performed by a single trained and experienced cardiac sonographer ([name]) using a Philips iE33 imaging system, Andover MA, blinded to the patients’ test results of the diagnostic work-up. Guidelines of the American Society of Echocardiography [19,20] will be followed to assess structural and functional cardiac properties. The left ventricular ejection fraction (LVEF) will be assessed quantitatively, or semi-quantitatively when necessary. Multiple diastolic parameters will be measured, including pulsed-wave Doppler of the mitral and pulmonary venous inflow and tissue Doppler imaging of the mitral annulus motion. The ratio of peak early (E) diastolic filling velocity to peak of atrial (A) contraction (E/A ratio) will be calculated. The early diastolic mitral annular velocity (e’) will be determined at the septal and lateral wall, and the average of both velocities will be used to calculate the E/e’ ratio.

Participants will register the experienced burden of the aforementioned investigations on a visual analogue scale (VAS) (0 = not burdening at all, 10 = extremely burdening).

The participating GPs will receive a first preliminary conclusion about the presence or absence of HF, based on all available information from the diagnostic work up. GPs will be asked to initiate treatment in patients with HF according to their allocation (intervention or care as usual). An expert panel consisting of two cardiologists and a GP will finally establish or exclude HF.

Participants with a newly established diagnosis of HF will be asked to perform a 6MWT [21], and again after six months of follow-up. All participants will be asked to fill out the HRQoL questionnaires again six months after the diagnostic assessment.

In addition, information about medication, HF related appointments with the GP, HF related referrals to the cardiologist, and HF related hospitalization rates will be extracted from the electronic medical files at the GP’s office during 12 months of follow-up.

### Intervention

Patients with newly diagnosed HF will participate in the cluster randomize trial, except for those having a potentially treatable cause of their HF; they will immediately be referred to a cardiologist. All other HF patients will receive either care as usual or management guided by a structured up-titration scheme (intervention) by their own GP.

The GPs randomly allocated to the intervention group will receive a half-day training in the management of HF and the practical application of an up-titration scheme for HF-REF and HF-PEF separately, based on the Dutch GPs’ heart failure guideline (NHG-standaard Hartfalen 2005) [22], a Dutch equivalent of the recent ESC Guideline on heart failure [4].

In patients with newly established HF-REF, the up-titration scheme will start with a combination of a diuretic and an ACE-inhibitor, or in case of intolerance to an ACE-inhibitor an ARB. In case of acceptable blood pressures, ACE-inhibitors will be further up-titrated until half of the recommended dose. When patients are in euvolemic state and there are no contra-indications, GPs will then start with up-titration of a beta-blocker. The dosage of the beta-blocker will be increased to either the maximal recommended dose or the maximal tolerated dose. After the up-titration period of the beta-blocker, the GP will try to further increase the dosage of the ACE-inhibitor up to either the maximal recommended dose or maximal tolerated dose.

Patients with newly established HF-PEF will receive optimal blood pressure treatment. An ACE-inhibitor (or ARB) or low dosages of diuretics will be prescribed. In case of tachycardia such as in atrial fibrillation, the GP will aim to regulate the heart rate, preferably with a beta-blocker. A diuretic will also be prescribed if signs or symptoms of fluid or salt retention are present. See Figure 2 for a simplified version of the initiation- and up-titration scheme for HF patients, and Additional file 1 for the full content of the scheme.

